Antibiotic paste, is a mixture of metronidazole and ciprofloxacin, which is used as intra-canal medication for disinfection of necrotic teeth. Antibiotic paste has been reported to be effective at reducing bacterial numbers in the root canal systems of infected teeth (Mohammadi & Abbott 2009). When most commonly used medicaments fail in eliminating the symptoms, then antibiotic paste could be used clinically in the treatment of teeth with large periradicular lesions (Taneja & Kumari 2012).

Objectives of the present study: To test the null hypothesis whether the use of antibiotic paste will be more effective in reduction of pain and endotoxins than calcium hydroxide, or will these paste have disadvantages and complains more than the traditional method if used.

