# Trial Design:

# Type: Parallel randomized clinical trial

# Allocation ratio: 1:1

# Framework: Superiority

# Aim of the Study:

To assess the ability of antibiotic paste versus calcium hydroxide used as intra-canal medication in reducing pain and level of endotoxins in necrotic teeth with apical periodontitis.

- **PICO approach**

**P:** **population**, patients with non-vital permanent teeth with apical periodontitis.

**I: intervention,** antibiotic paste intra-canal medication.

**C: control,** calcium hydroxide intra-canal medication.

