**O: outcomes:**

|  | **Outcome measure** | **Tool for measurement** | **Unit of measurement** |
| --- | --- | --- | --- |
| Primary | Postoperative Pain | Numerical rating scale (Brunelli et al, 2010) | Ordinal |
| Secondary | Quantification of endotoxins | LAL assay | EU/mL |

Postoperative pain will be measured using Numerical Rating Scale (NRS) after 6, 12, 24 and 48 hours from the end of root canal obturation **(Evaristo et al. 2013)**

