# Research question:

In patients with necrotic teeth and apical periodontitis would the use of antibiotic paste be more effective in reduction of pain and endotoxins than calcium hydroxide or not?

- **Subjects and Methods:**

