# 0 reading represents “no pain”

# 3 readings represent “mild pain”

# 4- 6 readings represent “moderate pain”

# 7- 10 readings represent “severe pain”

Secondary outcomes will be collected by the operator by commercial standard kit then stored at -80^0^ C so that all samples would be processed at the same time by LAL assay for quantification of bacterial endotoxins.

- **Statistical analysis:**

Data will be analyzed using IBM SPSS advanced statistics (Statistical Package for Social Sciences), version 21 (SPSS Inc., Chicago, IL). The level of endotoxins will be described as mean and standard deviation. The level of pain will be described as median and range or interquartile range, as appropriate. The level of endotoxins will be explored for normality using Kolmogrov-Smirnov test and Shapiro-Wilk test. If the exploration of data reveals that the collected values are normally distributed, a 2-way ANOVA with repeated measures will be performed to compare between the 2 groups and the change with time. If the interaction between the groups and time is found to be significant, a 1-way repeated measures ANOVA will be used to examine significant differences between time periods within each of the two groups. The Student’s t-test will be performed to test the significance between the two groups at each time period. If the exploration of data reveals that the level of endotoxins is not normally distributed and for the analyses of the pain score, Mann-Whitney U test will be performed to test the significance between the 2 groups at each time period. Friedman’s test followed by multiple comparisons test will be performed to test the significance between the 4 time periods within each group. In addition, correction of p-value will be done using Bonferroni adjustment to avoid hyperinflation of type 1 error that arises from multiple comparisons. A p-value less than or equal to 0.05 will be considered statistically significant. All tests will be two tailed. The effect size will be measured using standardized mean difference.

- **Data monitoring:**

There will not be a Data Monitoring Committee for the following reasons:

- Interim analysis is not involved in the trial so periodic inspection of the accumulating outcome data is not required.
- Short duration of the trial.
- Minimal risks of the trial.
- **Harms**

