Adverse events are minimal or rare. However, if any harm is seen in the participants either in intervention or control groups they will be recorded and reported at the end of the trial. It will be documented as part of routine monitoring not as outcome. The treatment will be according to the harm:

- Pain: administration of Analgesics.
- Swelling: hot fomentation, mouth rinse with salty warm water, antibiotic will be administrated.
- Allergic reaction: referral for a physician for corticosteroid therapy.
- Auditing

In this trial, auditing will be performed in order to preserve the integrity of the trial, the audit will review the processes of participant enrolment, consent, eligibility, allocation to study groups and adherence to trial interventions and policies to protect participants.

- **Ethics and dissemination**
- **Research ethics approval:**
- This protocol and the template informed consent form will be reviewed by the Ethics Committee of Scientific Research, faculty of oral and dental medicine, Cairo University.
- Each of the protocol, informed consent forms in Arabic and English language, recruitment materials and any modifications will be done later on also will be reviewed and approved by the ethical review Committee.
- **Protocol amendments:**

The ethical committees will notified any administrative changes or modifications of the protocol or modification of registered online protocol.

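### The objective asks whether the paste brings more disadvantages and complaints than calcium hydroxide, but harms are excluded as an outcome, so the non-pain part of that question has no planned comparison between arms

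*Protocol*

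**What the plan says.** The Protocol states its purpose in several places, and they do not agree.

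- **Objectives of the present study (end of the Introduction).** After efficacy on pain and endotoxins, the sentence adds "or will these paste have disadvantages and complains more than the traditional method if used".
- **Aim of the Study.** Efficacy only: "in reducing pain and level of endotoxins in necrotic teeth with apical periodontitis". The opening sentence of the Sample Size section repeats this aim.
- **Research question.** Efficacy only: "would the use of antibiotic paste be more effective in reduction of pain and endotoxins than calcium hydroxide or not".
- **Outcome table (PICO, outcomes).** Two rows: "Primary | Postoperative Pain" and "Secondary | Quantification of endotoxins".
- **Statistical analysis.** Between-group tests are given for endotoxins and pain. For pain: "for the analyses of the pain score, Mann-Whitney U test will be performed to test the significance between the 2 groups at each time period". No test or summary is named for any other event.
- **Harms.** The section promises that "if any harm is seen in the participants either in intervention or control groups they will be recorded and reported at the end of the" study. The next sentence reads: "It will be documented as part of routine monitoring not as outcome". A list of three harms follows (pain, swelling, allergic reaction), each with the way it will be managed.

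**The concern.** The clause in the objective is a between-arm question, because it asks whether one medicament has more disadvantages than the other. The Harms section does not merely leave that question open. It rules harms out as an outcome. A later analysis plan could not repair this alone: adding the comparison as an outcome would contradict the Harms section, and omitting it would leave part of the objective unanswered.

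The trial compares a newer medicament with the traditional one. A favourable pain result could be published with no pre-specified answer on disadvantages. The Harms section already presumes that adverse events are minimal or rare, so a handful of informally noted events, or none, could be read as confirming that. The operator opens the envelope and so knows the allocation. The recording rule depends on a harm being noticed, which leaves room for unequal recording between arms.

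**Working it through.** The point is mainly textual. The Protocol gives no figure for harms, so there is none to reproduce.

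**Step 1. Match each part of the objective to an outcome and a comparison.**

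| Part of the objective | Listed outcome | Between-group comparison planned |
| --- | --- | --- |
| Pain | Yes, primary | Yes, Mann-Whitney at each time period |
| Endotoxins | Yes, secondary | Yes, t-test or Mann-Whitney at each time period |
| Complaints in the form of pain | Covered by the primary outcome | Yes |
| Other disadvantages and complaints (swelling, allergic reaction, need for analgesics) | No, expressly excluded | None stated |

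Only the last row is unmatched.

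**Step 2. Check whether the data would exist.** The commitment is to record harms that are seen, in either group, and to report them. The three listed items state how each harm is treated, not what is captured on a form. The readable parts of the pain scale chart (Figures 6 and 7) and the assessor chart (Figure 8) carry pain scores only. The baseline report forms are figures that are not shown. No readable text provides for logging analgesic intake.

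**Step 3. Check the time window.** The outcome table section times pain from the end of obturation. The procedural steps place the 6 to 48 hour recordings after the medication is inserted and before the 7-day visit. The Participant timeline has the charts returned at the second visit. Obturation takes place at that second visit, so these statements cannot all hold. A harms window ending at the second visit would miss events after obturation if the outcome table's timing applies.

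**Step 4. What the numbers could show.** The Sample Size section gives 18 per arm. It also gives 28 in total before the allowance for losses, which is 28/2 = 14 per arm. For zero events in n patients, the exact two-sided 95% upper limit is 1 − 0.025^(1/n):

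- n = 18: 1 − 0.025^(1/18) = 18.5%
- n = 14: 1 − 0.025^(1/14) = 23.2%

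The Protocol states no harm rates, so the rates below are assumptions. Power of the two-sided Fisher test at 5%:

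| Assumed rates | 18 per arm | 14 per arm |
| --- | --- | --- |
| 5% v 20% | 0.13 | 0.07 |
| 5% v 30% | 0.38 | 0.24 |
| 5% v 40% | 0.65 | 0.48 |

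At either size, with no events in one arm, at least 5 are needed in the other for p ≤ 0.05. A harms comparison in this trial can only be descriptive.

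**The case against.** The strongest reply is that one loosely worded clause is the outlier. The aim, the research question and the aim restated under Sample Size all name only pain and endotoxins, and the outcome table matches them. On that view the repair is editorial. This stands as far as it goes, and it is why deleting the clause is an acceptable remedy. It does not remove the conflict while the clause remains in the objective.

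A reader might infer that half of the objective cannot be answered. The documents do not support that, because pain is the most obvious complaint and is compared between arms at every time period.

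A reader might also infer that harms will go unreported or cannot be shown by arm. The Harms section commits to recording and reporting harm in either group, and excluding harms as an outcome does not forbid a count by arm. What is missing is a planned comparison, not all reporting.

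A third tempting inference is that these events are already captured, so a comparison costs nothing. Step 2 shows otherwise: the list concerns management, and the readable charts have no field for these events. Without active questioning, an exact interval would put a precise range around events that happened to be noticed.

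Finally, analgesics could influence the pain scores. That is a separate question about the primary outcome. A harms row would not settle it, and it adds no weight here.

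**Conclusion.** The point holds in limited form. The objective contains a between-arm question on disadvantages and complaints, the Harms section excludes harms as an outcome, and comparisons are planned only for pain and endotoxins. The gap is the non-pain part of the clause. It should be corrected, but it does not touch the primary analysis, the endotoxin analysis or the sample size.

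The upper limits of 18.5% and 23.2% do not measure the inconsistency. They show how little an absence of events could establish, and they assume that all 18 or 14 patients per arm are actually asked about the events. The power figures rest on assumed event rates and serve only to show that no inferential claim on harms is realistic.

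**What to change.** Choose one of two routes.

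**Keep the question.**

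1. In Harms, delete the words that exclude harms as an outcome.
2. Add one descriptive secondary outcome to the outcome table: the number of patients per arm with swelling, with an allergic reaction, and with analgesic use.
3. Ask about these in the same way in both arms, through the last pain assessment. Before that window can be fixed, reconcile the timing of the pain assessments between the outcome table section, the procedural steps and the Participant timeline.
4. Report counts per arm with exact 95% confidence intervals and the between-arm difference. Claim no power, and show the upper limit where no events occur.

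The cost is one row in the outcome table, one line on the patient or assessor chart and one summary table. No change to sample size, randomization or treatment follows.

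**Drop the question.** Remove the disadvantages clause from the objective so that it agrees with the aim, the research question and the Sample Size section, and draw no comparative conclusion on harms. The cost is one edited sentence. The existing commitment to record and report harms in both groups stays.

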A 2-stage access cavity preparation will be performed. The first stage involved the removal of caries without exposure of the pulp chamber by using a high-speed diamond bur. In the second stage, before entering the pulp chamber, the access cavity will be disinfected according to the decontamination protocol described previously. A new bur will be used to access the canal.

1. 1^st^ sample:-

The first endotoxin sample will be taken by introducing the paper points^[[2]](#footnote-2)^ into the full length of the canal (determined by radiographs and apex locator^[[3]](#footnote-3)^) and retaining them in position for 60 seconds. Next, the paper points will be placed in a glass tube and stored at -80^0^C for the LAL assay.

1. Preparation:-

-The root canals will be prepared with Gates-Glidden drills^[[4]](#footnote-4)^ sizes 4, 3 and 2 for the coronal part, and rotary Irace instruments^[[5]](#footnote-5)^ using an endodontic motor^[[6]](#footnote-6)^ with adjusted torque and speed according to the manufacturer's instructions. The rotary files will be introduced inside the canal using EDTA gel^[[7]](#footnote-7)^.

-Before the use of each instrument, irrigation with a syringe (27-G needle) Containing 3ml 2.5% sodium hypochlorite^[[8]](#footnote-8)^.

- Subsequently, 5% sodium thiosulfate will be used to inactivate NaOCl. Then, 5ml saline solution to wash the canal.

1. 2^nd^ sample:-

The second endotoxin sample will be taken as previously described just after the irrigation with saline solution.

1. Intracanal medication:-

The canals will be dried with paper points and filled with intracanal medication plugged into the canal by using Lentulo spiral^[[9]](#footnote-9)^ . The access cavities will be properly filled with Cavit^[[10]](#footnote-10)^.

- **Control group:** Ca (OH)_2_ Paste.
- **Experimental group:** antibiotic paste (ciprofloxacin, metronidazole)

1. The patient will be instructed to record his/her pain level on the pain scale chart after 6 h, 12 h, 24 h and 48 h.
2. 3^rd^ sample:-

After 7 days of intracanal medication, the canal will be accessed under rubber dam isolation by using the protocol for disinfection described previously. The medication will be removed, the final endotoxin sample will be taken just after the irrigation with saline solution.

1. Obturation:-

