**Assessor Chart**

**Patient No.:**

| Examiner Assignment | Score | Date | Follow up by hours |
| --- | --- | --- | --- |
|  |  |  | 6 |
|  |  |  | 12 |
|  |  |  | 24 |
|  |  |  | 48 |

**Figure(8) :** The assessor chart

**
[figure not shown]
**

**Figure(9) :** The informed consent form given to each patient.

[figure not shown]

**Figure(10) :** The informed consent form given to each patient.

1. #### Carpule3M™ ESPE™ Ubistesin™ Articaine HCI 4% & Adrenaline 1:100,000 3M Australia

   [↑](#footnote-ref-1)
2. Dentsply Maillefer, Ballaigues, Switzerland [↑](#footnote-ref-2)
3. Root ZX, J.Morita USA, Irvine, CA. [↑](#footnote-ref-3)
4. Mani, Tochigi, Japan [↑](#footnote-ref-4)
5. **FKG Dentaire SA,switzerland.** [↑](#footnote-ref-5)
6. ^5^X-Smart, DentsplyMaillefer, USA.

   6MD-Chelcream, META BIOMED CO.,LTD, Korea.

   7Household Cleaning Products Of Egypt, 10th Of Ramadan, Egypt [↑](#footnote-ref-6)
7. [↑](#footnote-ref-7)
8. . [↑](#footnote-ref-8)
9. Dentsply Maillefer, Ballaigues, Switzerland [↑](#footnote-ref-9)
10. 3M ESPE, Seefeld, Germany [↑](#footnote-ref-10)
11. **FKG Dentaire SA,switzerland** [↑](#footnote-ref-11)
12. ^4^ADSEAL, META BIOMED CO.,LTD, Korea. [↑](#footnote-ref-12)
13. G*Power program (University of Düsseldorf, Düsseldorf, Germany). Faul, F., Erdfelder, E., Lang, A.-G., & Buchner, A. (2007). G*Power 3: A flexible statistical power analysis program for the social, behavioral, and biomedical sciences. Behavior Research Methods, 39, 175-191. [↑](#footnote-ref-13)

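### Analgesics are allowed for the symptom that is the primary outcome, but the plan has no entry for intake beside the pain scores and the pain analysis ignores it

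*Protocol*

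**What the plan says.** **Treatment of pain.** The Harms section lists events and their treatment. For pain it says "Pain: administration of Analgesics"; for swelling, "Swelling: hot fomentation, mouth rinse with salty warm water, antibiotic will be administrated". It sets no time limit on either.

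**Recording of harms.** The same section promises a record and a report at study end for both arms ("if any harm is seen in the participants either in intervention or control groups they will be recorded and reported at the end of the" …), and adds "It will be documented as part of routine monitoring not as outcome".

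**Primary outcome.** The outcomes table names postoperative pain, and the note below it reads "Postoperative pain will be measured using Numerical Rating Scale (NRS) after 6, 12, 24 and 48 hours from the end of root canal obturation". In the procedural steps the instruction comes after the medicament is placed and before the day-7 visit: "The patient will be instructed to record his/her pain level on the pain scale chart after 6 h, 12 h, 24 h and 48 h". The Participant timeline has patients hand in their charts at the second visit.

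**Forms.** The readable text of the pain chart (Figures 6 and 7) shows a training item, a preoperative item and the four timed items. The columns of the assessor chart (Figure 8) are "Examiner Assignment | Score | Date | Follow up by hours".

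**Analysis.** The Statistical analysis section applies a Mann-Whitney U test to pain between the groups at each time, two-sided at 0.05. It does not mention analgesics.

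**Objective.** The Introduction also asks "will these paste have disadvantages and complains more than the traditional method if used".

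**The concern.** One symptom is both the endpoint and the reason for giving a treatment that lowers the endpoint. If the plan is followed as written, a score of 2 after an analgesic and a score of 2 without one enter the test as the same value, and nothing on the readable charts tells them apart.

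This is more than a detail that a statistical analysis plan could supply later. Such a plan can say how readings after an analgesic are handled, but it cannot recover intake times that were never written down. Patients score themselves at home between visits, so what is not on the chart is unlikely to be recoverable score by score. At stake are the size of the pain difference, and possibly its direction, in a superiority trial of 36 patients.

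**Working it through.** **What the documents fix.** 18 patients per arm; 0-10 scale; Mann-Whitney test, two-sided 0.05. The Sample Size section gives minimal clinical differences of 3.5 (24 h) and 4.5 (48 h). It gives no analgesic uptake, trigger or effect and makes no allowance for them, so the plan has no figure of its own to reproduce here. Everything below is an illustration under assumed inputs.

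**Formula.** Let π be the share of an arm at or above the trigger score, p the share of those who take an analgesic, and r the drop in the next reading (no larger than the trigger score). The control-minus-experimental difference changes as

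observed = true − r × (p_C × π_C − p_E × π_E).

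**Case 1: same rule in both arms, means 5 (control) and 3, SD 2.5, trigger 4, r = 3.** A rounded score of 4 or more means a latent value of at least 3.5.
- π_C = P(Z ≥ (3.5 − 5)/2.5) = P(Z ≥ −0.6) = 0.726
- π_E = P(Z ≥ (3.5 − 3)/2.5) = P(Z ≥ 0.2) = 0.421
- π_C − π_E = 0.305
- After rounding and truncation to 0-10, the true difference is 1.86.
- 50% uptake: 1.86 − 3 × 0.5 × 0.305 = 1.40, a loss of 0.46/1.86 = 25%.
- 80% uptake: 1.86 − 3 × 0.8 × 0.305 = 1.13 (simulated 1.12), a loss of about 40%.

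Simulated power at one time point (4,000 trials, 18 per arm) falls from about 0.61 to 0.46 (50% uptake) and to 0.40-0.41 (80%). If only scores of 7 or more trigger use, at 80% uptake, it falls to about 0.54.

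**Case 2: same rule, means 6 and 2.5, SD 2.5.** This takes the protocol's 3.5 as a difference in means.
- π_C = P(Z ≥ −1) = 0.841; π_E = P(Z ≥ 0.4) = 0.345; π_C − π_E = 0.496
- The true difference after truncation is about 3.24. It becomes 3.24 − 1.5 × 0.496 = 2.50 at 50% uptake and 3.24 − 2.4 × 0.496 = 2.05 at 80%, losses of about 23% and 37%.
- Power falls from about 0.98 to 0.90 (50%) and 0.87 (80%).

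**Case 3: no true difference, unequal uptake at equal pain.** Both means 5, SD 2.5, trigger 4, r = 3, uptake 30% in control and 80% in experimental.
- Observed difference = 0 − 3 × (0.3 × 0.726 − 0.8 × 0.726) = 3 × 0.5 × 0.726 = 1.09 points in favour of the experimental arm.
- Simulated false rejection is about 28%, against a nominal 5%. With the two rates swapped, the false difference favours control.

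**A second set of assumptions.** With 14 evaluable per arm (28 in total, the target before the allowance for losses), means 5 and 3, SD 2, equal uptake, triggers of 4 or 7, and either 50% uptake with a 2-point drop or 80% with a 3-point drop, the difference falls from about 1.95 to 1.05-1.76 and power from about 0.70 to 0.35-0.67.

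**Does ranking users worst repair it?** Only partly. In Case 1 power is about 0.47 at both uptake rates, against 0.46 and 0.40-0.41 as recorded. At trigger 7 and 80% uptake it is about 0.61 against 0.54. In Case 3 it still rejects about 29% of the time, now against the arm with more users. It is useful as a contrast to the as-recorded analysis, not as a correction.

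**The case against.** **Harms are recorded.** The Harms section promises a record and report for both groups, pain is on its list, and several figures are not shown. A reader might infer that analgesic use is recorded nowhere; the documents do not support that. What stands is narrower: no readable outcome form has an entry for it, and nothing requires that intake or its time be linked to a score.

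**Direction.** A reader might infer that the bias must run toward no difference because the arm with more pain takes more analgesic. The protocol gives no uptake figures. Blinding covers participants and the assessor, while the operator opens the envelope and places the medicament, so equal uptake at equal pain cannot be assumed. Case 3 shows that the bias can create a difference.

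**Size.** The large loss of power belongs to an assumed 2-point effect. At the protocol's own 3.5 points it is modest. This objection stands, and both cases should be read together.

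**As-recorded scores are legitimate.** Comparing pain under each medicament with analgesics used as needed is a sensible question, and the choice among strategies is commonly left to the analysis plan. That argues against imposing an imputation as the primary analysis. It does not argue against collecting the data that any of the strategies needs for interpretation.

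**The disadvantages question.** A reader might infer that it goes unanswered. Harms in both groups are to be reported, so that is too strong. What is missing is a stated comparison between arms, and harms are expressly not an outcome.

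**Antibiotics for swelling.** A reader might infer that these alter the day-7 endotoxin sample. No passage says so or gives a size. A note of use is worth having, but no effect can be claimed.

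**Conclusion.** The point holds in a limited form. Analgesics are permitted, with no limit on timing, for the symptom that is the primary outcome; the readable charts have no place for intake or time; and the stated analysis ignores it. The pain comparison can therefore be distorted to an extent that could not be judged afterwards.

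Under one pain-driven rule in both arms, the observed difference shrinks by about 25-40% in Case 1, with power falling from about 0.61 to 0.40-0.46, and by about 23-37% in Case 2, with power falling from about 0.98 to 0.87-0.90. With unequal uptake the error can go either way. All of these figures rest on assumed means, SD, trigger, uptake and drop, at a single time point with no multiplicity adjustment.

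Two inconsistencies belong to the same point. The outcomes section counts hours from obturation, whereas the procedural steps and the Participant timeline place the readings before the second visit, so the window in which intake matters is not defined. The Introduction's question about disadvantages and the Harms section's statement that harms are not an outcome also need to be reconciled.

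**What to change.** Leave clinical care as it is and change only recording, analysis and reporting.

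1. Add to the patient chart and to Figure 8, for each interval, a yes/no and a time entry for any analgesic, and a note of any systemic antibiotic.
2. Report analgesic use by arm and time point.
3. Keep the Mann-Whitney test on as-recorded scores. Add one pre-stated sensitivity analysis that accounts for readings taken after an analgesic, for example ranking them worst, and say that it does not correct for unequal uptake.
4. Report the harms already recorded by arm, so that the Introduction and the Harms section agree.
5. Reconcile the outcomes section with the procedural steps and the Participant timeline on the start of the 6-48 hour clock, and define the intake window from it.

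The cost is a few extra fields on existing forms, a paragraph of analysis text, slightly more work for patients and one more analysis. It must be done before enrolment, because intake that was not recorded cannot be reconstructed reliably.
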